**FIGURE 2 brb371017-fig-0002:**
[figure not shown]
Simulation depicting the normalized magnetic field applied by rTMS following our protocol, simulated using SimNIBS, highlighting the maximal induced field over the left DLPFC.

### Post Intervention Assessment

1.4

#### Questionnaires

1.4.1

After 10 rTMS sessions, we will perform the cognitive tests again under the same conditions. For educated individuals, we will use MoCA exams, and for uneducated subjects (0 years of schooling), we will only use the MMSE test again. If a participant's MMSE or MoCA score increases after the TMS, they will be considered a responder. Conversely, if their score decreases or there are no changes, they will be classified as a non‐responder (Kayasandik et al. 2022).

We will utilize the minimal clinically important difference (MCID) to evaluate significant changes in test scores. According to the MCID, an increase of 3 points or 10% (Borland et al. 2022; Watt et al. 2021) in the MMSE indicates cognitive improvement (Borland et al. 2022; Watt et al. 2021). The MCID for the MoCA may vary, but we will consider a 1‐point increase as a sign of cognitive improvement (Lindvall et al. 2024). After completing the work, patients will receive free visits from the psychosomatic fellowship to continue their treatment in accordance with ethical principles.

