**Design:**

This multi‐center, assessor‐blinded clinical trial will examine QEEG biomarkers as predictors of rTMS treatment responsiveness in 25 patients with mild cognitive impairment (MCI). Adults aged 60 years or older will undergo cognitive assessments using the Montreal Cognitive Assessment (MoCA) or mini‐mental state examination (MMSE) and have an electroencephalography (EEG) recording. Participants will complete 10 rTMS sessions targeting the left DLPFC over 2 weeks, with 2000 pulses per session at 20 Hz. Cognitive tests will be repeated post‐treatment, and participants will be classified as responders or non‐responders based on cognitive changes, then baseline QEEG parameters will be compared between the two groups. The primary endpoint is the proportion of responders at ten sessions after rTMS (score post‐intervention > score pre‐intervention = responder, according to the minimal clinically important difference (MCID) threshold (i.e., an increase of at least 3 points or 10% on the MMSE, or an increase of at least 1 point on the MoCA); score post‐intervention ≤ score pre‐intervention = non‐responder). The secondary endpoints are the differences in baseline QEEG features between responders and non‐responders.

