#### Questionnaire

1.2.1

The most popular test for diagnosing dementia is the MMSE, whereas the Montreal Cognitive Assessment (MoCA) is a very accurate test for mild cognitive impairment. To assess volunteers' global cognition, we will use MMSE and MoCA.

Thirty questions make up the MMSE, which evaluates orientation (10 points), immediate recall (3 points), attention and calculation (5 points), recall (3 points), and language (9 points) (Seyedian et al. 2008; Abe et al. 2020).

Eight cognitive domains are evaluated by the thirty questions in the MoCA, which also include executive functions and visuospatial skills (5 points), attention (6 points), naming (3 points), abstract thinking (2 points) language (3 points), recall (5 points), and orientation (6 points) (Badrkhahan et al. 2020). Higher scores on the MMSE and MoCA indicate higher cognitive function; scores range from 0 to 30. Because of the nature of questionnaires, if participants are uneducated (0 year of schooling), we add 3 points to the score of MMSE. Range of the Farsi version of thr MMSE is 20 < MMSE < 24, indicating MCI (Delbari et al. 2024). Besides, in MOCA test, Because the nature of questionnaires, if the subjects have less than 12 years of schooling (1‐11 years of schooling), we add 1 point to the score and range of 22 < MoCA < 26 indicate MCI (Zhao et al. 2011). For educated individuals, we will use MOCA exams. and for uneducated subjects (0 years of schooling), we will only use the MMSE test.

Finally, a history and mental state assessment by a psychiatrist based on the Diagnostic and Statistical Manual of Mental Disorders, fifth edition (DSM‐V), is crucial because the decline or stability of cognitive performance compared to the past is the most important issue (Edition 2013; Kaplan 2015).

MMSE and MoCA tests will be repeated at the end of the treatment to classify participants as responders or non‐responders to the intervention. We will use the minimal clinically important difference (MCID), based on clinically meaningful changes in cognitive test scores. The MCID denotes the smallest change in score perceived as beneficial or significant by patients or clinicians. Detailed thresholds for the MMSE and MoCA tests are comprehensively described in the post‐intervention assessment section.

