### Group Classification

1.5

MCI with 22 < MoCA < 26 or 20 < MMSE < 24 after 2 weeks of intervention and post‐assessments will be divided into two groups (score post‐intervention > score pre intervention = responder, according to MCID threshold (i.e., an increase of at least 3 points or 10% on the MMSE, or an increase of at least 1 point on the MoCA); score post‐intervention ≤ score pre‐intervention = non‐responder).

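### The responder rule contradicts itself: MMSE gains of 1 or 2 points are a response in section 1.4.1 and belong to neither group in section 1.5 and the abstract

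*Protocol article*

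**What the plan says.** The protocol article states the responder rule in three places.

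- **Section 1.4.1, first paragraph.** If the "MMSE or MoCA score increases after the TMS, they will be considered a responder". For the opposite group: "Conversely, if their score decreases or there are no changes, they will be classified as a" non-responder. Any rise counts, and the two groups together cover every outcome.
- **Section 1.4.1, second paragraph.** A minimal clinically important difference (MCID) is introduced. For the MMSE it is "an increase of 3 points or 10" percent. For the MoCA, "we will consider a 1‐point increase as a sign of cognitive improvement".
- **Section 1.5 and the abstract (Design).** A responder must reach the MCID: "an increase of at least 3 points or 10% on the MMSE, or an increase of at least 1 point on the MoCA". The other group is defined as "score post‐intervention ≤ score pre‐intervention = non‐responder".

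Section 1.5 says that participants are split into two groups. Section 1.6.1 makes the primary endpoint the proportion of responders by MCID.

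Sections 1.2.1 and 1.4.1 reserve the MMSE for participants with no schooling; everyone else is classified on the MoCA. For the unschooled, section 1.2.1 adds a correction: "we add 3 points to the score of MMSE". It gives the eligible MMSE range as strictly between 20 and 24.

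**The concern.** A responder rule has to place every participant in exactly one group. Here one rule is complete but ignores the MCID, and the other applies the MCID but leaves a gap between its two definitions. An MMSE participant who improves by less than the MCID could be labelled a responder (section 1.4.1), a non-responder (by inference, because section 1.5 wants two groups) or left out (section 1.5 read literally).

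The label carries most of the analysis. It is the primary endpoint, it forms the groups for the cognitive comparisons in section 1.7.1, and it is the outcome for the QEEG tests and for every AUC, sensitivity, specificity and likelihood ratio in section 1.7.2. While more than one reading is open, the choice could be made after the scores and EEG data have been seen.

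**Working it through.** There is no figure in the plan to reproduce. The check is to apply both rules to every possible change score and then gauge how many participants could be affected.

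**Inputs from the article.** N = 25. Eligible MMSE scores are the integers 21, 22 and 23. Three points are added for no schooling, so if the range applies to the corrected score, the raw scores are 18, 19 and 20. The MCID is 3 points or 10% on the MMSE and 1 point on the MoCA.

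**Step 1: what 10% means in points.** The 3-point correction cancels in the change score but not in the base of the percentage.

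- Adjusted base: 0.10 × 21, 22, 23 = 2.1, 2.2, 2.3. With whole-point scores a gain of 3 is needed, so the 10% criterion adds nothing.
- Raw base: 0.10 × 18, 19, 20 = 1.8, 1.9, 2.0. A gain of 2 is enough at every baseline.
- Full scale as base: 0.10 × 30 = 3.0. A gain of 3 is needed.

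**Step 2: both rules applied to each MMSE change.**

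| MMSE change | 1.4.1, any rise | 1.5 and abstract, 10% of adjusted score | 1.5 and abstract, 10% of raw score |
|---|---|---|---|
| 0 or below | non-responder | non-responder | non-responder |
| +1 | responder | no group | no group |
| +2 | responder | no group | responder |
| +3 or more | responder | responder | responder |

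**Step 3: the MoCA.** With whole-point scores, any rise and a rise of at least 1 point are the same thing, and no rise is the exact complement. The rules agree and there is no gap.

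**Step 4: how often an MMSE gain of 1 or 2 would occur.** The article gives no change SD, mean change or number of unschooled participants, so these are assumptions. Treat the change as normal with mean m and SD s, rounded to whole points:

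P(+1 or +2) = Φ((2.5 − m)/s) − Φ((0.5 − m)/s)

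Over m = 0 to 1 and s = 1.5 to 2.5:

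- lowest, m = 0, s = 2.5: Φ(1.0) − Φ(0.2) = 0.262
- highest, m = 1, s = 1.5: Φ(1.0) − Φ(−0.333) = 0.472

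Expected number affected, by number of unschooled participants:

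| Unschooled, of 25 | Low (× 0.262) | High (× 0.472) |
|---|---|---|
| 0 | 0 | 0 |
| 3 | 0.8 | 1.4 |
| 5 | 1.3 | 2.4 |
| 8 | 2.1 | 3.8 |
| 12 | 3.1 | 5.7 |

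With 8 unschooled participants that is about 2 to 4 labels: 2/25 = 8% to 4/25 = 16% of the sample.

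**Step 5: effect on the primary proportion.** Each participant who moves between responder and non-responder shifts it by 1/25 = 4 percentage points. For illustration, suppose 10 participants reach the MCID and 3 more gain 1 or 2 MMSE points:

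- MCID rule, all others non-responders: 10/25 = 40%
- any rise counts: 13/25 = 52%
- participants without a group dropped: 10/22 = 45.5%

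**The case against.** The strongest reply is that the article's intention is clear. Sections 1.2.1, 1.5, 1.6.1 and 1.7.1 and the abstract all tie classification to the MCID, and the any-rise sentence in section 1.4.1 stands alone and is followed at once by the MCID paragraph. On that reading the responders are settled apart from the base of the 10%, and if all 25 form the denominator the primary proportion does not depend on what smaller gains are called. Since section 1.5 asks for two groups, a reader would naturally put smaller gains with the non-responders. The 10% question is also narrow: both the adjusted score and the 30-point scale give a 3-point threshold, and no section names the raw score as the base. Finally, only the unschooled are affected, their number may be small or zero, and this is an exploratory pilot that disclaims definitive testing.

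Much of this stands. The MCID is the more likely intention, the MoCA rule is sound, and the size of the effect depends on a stratum of unknown size. It does not remove the defect. The any-rise sentence is still in the text, and even with the MCID accepted, the written definition of a non-responder excludes MMSE gains below it. Whether those participants enter the QEEG comparison, and whether they count in the denominator, then rests on inference. The pilot status does not help much either: the Limitations section gives the study's purpose as effect-size estimates for later trials, and those estimates depend on this label.

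**Conclusion.** The concern holds. As written, the rule behind the primary endpoint is contradictory and not exhaustive for participants classified on the MMSE. A gain of 1 point is a response in section 1.4.1 and falls in no group in section 1.5 and the abstract. A gain of 2 points has the same problem on the adjusted score and becomes a response if 10% is taken of the raw score. That much follows from the text without any assumption, except that the eligibility range is read on the corrected score.

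The size does rest on assumptions. With an SD of 1.5–2.5 and a mean gain of 0–1 point, 26%–47% of MMSE-tested participants fall in the disputed zone. With 8 of 25 unschooled, about 2–4 labels depend on the reading. With no unschooled participants the effect is nil. In a sample of 25, already to be divided into two unequal groups, two to four labels are enough to matter for both the responder proportion and the QEEG contrasts. It should be corrected before anyone is classified.

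**What to change.** Put one rule, in the same words, in the abstract, section 1.4.1 and section 1.5: a responder is a participant whose change reaches the stated threshold for the test used; every other assessed participant, including one with a smaller gain, is a non-responder.

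To get there:

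- delete the any-rise sentence and its counterpart in section 1.4.1;
- replace the definition of a non-responder as no rise in score, in section 1.5 and the abstract;
- drop the 10% alternative, or state that it is taken on the education-adjusted score, where for eligible baselines it comes to 3 points.

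The cost is a wording change in three places, made before classification. It needs no extra participants, visits or data, and it leaves the MoCA classification as it is.

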#### Primary Endpoint

1.6.1

The primary endpoint is the proportion of responders according to MCID. Additionally, the primary analysis will determine which cognitive subdomains show the greatest therapeutic effects.

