#### Primary Endpoint

1.7.1

All assessors will be blinded to group allocation and receive data labeled as “group A” and “group B.” Statistical analyses will be conducted using StataNow18.5 (Stata Corp, College Station, TX, USA), adhering to CONSORT guidelines. Normality of continuous variables will be checked using skewness and kurtosis, with variables considered non‐normal if absolute skewness > 2 or kurtosis > 3. Baseline characteristics, including (sex, hyper‐lipidemia, hypothyroid, hyper‐tension, diabetes, smoking, ischemic heart disease, education, and age) will be compared between groups using Fisher's exact test for categorical variables and the Mann–Whitney *U* test for non‐normal continuous variables. For normally distributed continuous variables, between‐group comparisons will be performed using the independent samples t‐test.

Initially, paired *t*‐tests (a suitable transformation or non‐parametric test) or equivalents for non‐normal data will be used to evaluate overall pre‐ to post‐rTMS changes within all 25 participants, assessing global treatment efficacy and identifying cognitive subdomains demonstrating the greatest response. Subsequently, participants will be categorized into responders and non‐responders based on MCID criteria. Between‐group comparisons of cognitive scores and subdomains will then be performed using ANOVA for baseline and ANCOVA for post‐intervention outcomes, adjusting for baseline scores and potential confounders. Pre‐intervention values refer specifically to baseline cognitive test scores, totally and in each cognitive sub‐domain, and related continuous variables measured before rTMS, which serve as covariates in the analyses. The QEEG features are analyzed separately as part of the secondary endpoint assessment. For non‐normal variables, suitable transformation will be applied, and median differences with percentage changes reported. Marginal plots from ANCOVA will visualize adjusted group differences post‐intervention. This two‐stage analytical approach allows comprehensive evaluation of rTMS effects both globally and within clinically meaningful responder groups across cognitive domains.

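### The responder rule is stated in two conflicting ways, and an MMSE gain of 1 or 2 points is a responder under one and in neither class under the other

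*Protocol article*

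**What the plan says.** - **Section 1.4.1 (post-intervention questionnaires).** A participant whose "MMSE or MoCA score increases after the TMS, they will be considered a responder". The next sentence gives the complement: "Conversely, if their score decreases or there are no changes, they will be classified as a non‐responder". A separate paragraph then introduces the MCID as a sign of cognitive improvement, without tying it to the responder label.
- **Section 1.5 (Group Classification) and the abstract.** A responder must reach the MCID: "an increase of at least 3 points or 10% on the MMSE, or an increase of at least 1 point on the MoCA". The other group is still defined by direction alone: "score post‐intervention ≤ score pre‐intervention = non‐responder".
- **Section 1.6.1.** "The primary endpoint is the proportion of responders according to MCID".
- **Section 1.7.1.** "participants will be categorized into responders and non‐responders based on MCID criteria". Neither 1.6.1 nor 1.7.1 says where a gain below the MCID goes.
- **Section 1.2.1.** Patients with no schooling take only the MMSE, and "if participants are uneducated (0 year of schooling), we add 3 points to the score of MMSE". The eligible MMSE range lies strictly between 20 and 24. The section also refers the reader to the post-intervention assessment section for the detailed thresholds.

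**The concern.** Section 1.4.1 classifies on direction of change. Section 1.5 classifies responders on a threshold and non-responders on direction. The two sections therefore disagree, and the two classes in 1.5 do not cover everyone: a patient can improve by less than the threshold and fit neither definition. A second ambiguity lies in the 10% alternative for the MMSE, because the article does not say whether the percentage is taken on the score before or after the 3 education points.

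The label sets the primary proportion. It also forms the two groups for the ANCOVA (1.7.1) and for the QEEG comparison and ROC analysis (1.7.2); sensitivity and specificity cannot be computed until every patient has a class. If the choice is made after the data are seen, it can follow the preferred result. All affected patients have no schooling, so the choice also alters the education mix of the two QEEG groups.

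**Working it through.** The article gives no figure to reproduce here, so the check applies the written rules to every eligible baseline.

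**Inputs from the article.** N = 25 (abstract). Eligible integer baselines are MMSE 21, 22, 23 and MoCA 23, 24, 25 (1.1.2, 1.2.1). MMSE-only patients have 0 years of schooling and receive 3 points (1.2.1). The range 21–23 is taken as the adjusted score, so the unadjusted score is 18–20.

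**MoCA.** Scores are integers, so any increase is at least 1 point. The rules agree at every change.

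**MMSE, percentage gain = gain / baseline.**

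| Gain | On adjusted score (21–23) | On unadjusted score (18–20) |
|---|---|---|
| +1 | 1/23 to 1/21 = 4.3–4.8% | 1/20 to 1/18 = 5.0–5.6% |
| +2 | 2/23 to 2/21 = 8.7–9.5% | 2/20 to 2/18 = 10.0–11.1% |
| +3 | 3/23 to 3/21 = 13.0–14.3% | 3/20 to 3/18 = 15.0–16.7% |

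**Resulting class.**

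| MMSE change | 1.4.1 | 1.5, 10% of adjusted | 1.5, 10% of unadjusted |
|---|---|---|---|
| 0 or lower | non-responder | non-responder | non-responder |
| +1 | responder | neither | neither |
| +2 | responder | neither | responder |
| +3 or more | responder | responder | responder |

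**Illustration (invented data).** Take 20 MoCA patients, 8 of them improved, and 5 MMSE patients with changes +3, +2, +1, 0, −1.

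- 1.4.1: 8 + 3 = 11 responders, 11/25 = 44%.
- 1.5, 10% of adjusted score: 8 + 1 = 9 responders and 2 unclassified. This is 9/25 = 36%, or 9/23 = 39% if the unclassified are left out.
- 1.5, 10% of unadjusted score: 8 + 2 = 10 responders and 1 unclassified, 10/25 = 40%.

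**Likely size.** The article does not give the number k of MMSE-tested patients, the retest SD or the mean gain m. Assumed: k = 3, 5 or 10; SD 1.5, 2 or 2.5 points; m = 0, 0.5 or 1 point; a normal change rounded to integers. Then

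P(gain of 1 or 2) = Φ((2.5 − m)/SD) − Φ((0.5 − m)/SD).

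- Lowest (m = 0, SD 2.5): Φ(1.0) − Φ(0.2) = 0.262.
- m = 0, SD 2: Φ(1.25) − Φ(0.25) = 0.296.
- Highest (m = 1, SD 1.5): Φ(1.0) − Φ(−0.33) = 0.472.

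| k | Patients affected (k × 0.262 to k × 0.472) | Shift in primary proportion (÷ 25) |
|---|---|---|
| 3 | 0.79–1.42 | 3.1–5.7 points |
| 5 | 1.31–2.36 | 5.2–9.4 points |
| 10 | 2.62–4.72 | 10.5–18.9 points |

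These shifts compare the any-increase rule with the MCID rule when +1 and +2 both fall short. If 10% of the unadjusted score applies, only +1 is affected and the shift is smaller.

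**The case against.** The strongest reply is that the intended rule can be inferred. The abstract and sections 1.2.1, 1.5, 1.6.1 and 1.7.1 all point to the MCID. Section 1.5 speaks of two groups and no third class is described, so a gain below the MCID would naturally be a non-responder. On that reading, 1.4.1 contains one loose sentence, and dropping patients from the denominator is not something the article proposes. The MMSE runs to 30, so 10% may simply restate 3 points; only taking the percentage on the unadjusted score lets a 2-point gain qualify. The size rests on assumed inputs, the study is an exploratory pilot, and the full protocol may settle the matter.

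Much of this is fair. The weight of the text does favour the MCID, the 10% ambiguity is the lesser part, and the magnitude is conditional. But no sentence assigns a gain below the MCID, and the only explicit definitions of non-responder exclude it. Section 1.2.1 sends the reader for thresholds to the very section that contains the any-increase rule. This is contradictory text, not detail left for another document. Pilot status does not remove the problem, because the study is meant to supply effect sizes for later trials and those depend on group membership.

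**Conclusion.** The concern holds. The written rules contradict each other for MMSE gains of 1 point, and for gains of 2 points unless the 10% is taken on the unadjusted score. The two classes in 1.5 and the abstract are not exhaustive. MoCA-tested patients are unaffected. Each affected patient is worth 4 percentage points on the primary endpoint; the range of about 3 to 19 points depends on the assumed number of MMSE-tested patients (3 to 10 of 25) and on the assumed retest distribution. If no patient without schooling is enrolled, there is no effect. The point should be corrected: it bears on the primary endpoint, is confined to a subgroup and is easy to put right.

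**What to change.** Use one rule, worded identically in the abstract, 1.4.1 and 1.5:

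- **Responder:** a gain of at least 3 points on the MMSE or at least 1 point on the MoCA, with the same education points added at both visits.
- **Non-responder:** every other participant with a post-treatment score, including MMSE gains of 1 or 2 points.

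Delete the two direction-only sentences in 1.4.1 and the at-or-below-baseline clause in the abstract and 1.5. Either drop the 10% alternative or state that it applies to the adjusted score; at baselines of 21–23 it then always means 3 points and changes nothing. Optionally, describe the non-responders by how many scored higher but below the threshold, the same, or lower.

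The cost is three or four sentences, with no new data, visits or patients. The responder proportion may come out lower than under the any-increase wording. Because the Study Design section describes recruitment and testing in the past tense, the change should be dated and its timing relative to data access stated.
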